**Methods**

Primary aim:

To collect high quality and relevant data regarding global surgery exposure for medical students across the world in order to establish an international framework

Secondary Aims:

To examine students’ awareness of the key messages of the Lancet Global Surgery Commission

To characterise the proportion of medical students who would want to be involved in global surgery in their future career

To ascertain perceived barriers to becoming involved in global surgery

Study Design

The International Survey Of Medical students Exposure to Relevant global Surgery (ISOMERS) study is an online, international, multi-centre, questionnaire-based study evaluating global surgery exposure and career aspirations among final year medical students across the world. Data will be collected on the demographics of participants, their exposure to global surgery, their awareness of the key messages of the Lancet Global Surgery Commission, and their career aspirations. The questionnaire will be disseminated by email and social media through collaborative university medical school and student networks, such as the network of InciSioN National Working Groups (NWGs) across the world. The generic collaborative method, and the benefits that participating students derive from it are based on previous well-documented literature.

Study Population

All medical schools across the world will be eligible to participate. Participant eligibility will be determined according to pre-specified criteria. Responses will be excluded if the participant did not meet the inclusion criteria or met the exclusion criteria. Participation rates will be calculated as the total number of eligible participants over the total number of final year medical students at participating medical schools. The minimum sample size required from our target population for a margin of error of 5% and a confidence level of 95% is 377 assuming a 50% response distribution for each question.

Inclusion criteria:

All final year medical students across the world

Exclusion criteria:

Listed as a collaborative author or named author on any publications from this study.

Primary Outcomes

The proportion of students that have had exposure to global surgery in each country.

The range of modalities utilised by medical students to gain exposure to global surgery.

The percentage of students that prefer each modality.

Secondary Outcomes

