The online questionnaire utilises a combination of the Likert scale, multiple choice options and free text questions in order to broaden the capture and improve granularity of the data. The questionnaire is divided into four major sections: background information, provision of global surgery teaching, knowledge about global surgery and career aspirations. All sections of the questionnaire must be completed for the answers to be deemed eligible. Following data collection, the data will be validated and analysed by the steering committee. The questionnaire has been sent to multiple medical students who were not involved in creating the data collection proforma. Their responses were evaluated for potential problems, and the questionnaire was updated to ensure the questions were relevant, comprehensive and accessible.

Medical schools will be able to request for their own specific data and the analysis done on said data from the ISOMERS steering committee following study completion. InciSioN NWGs will be able to request for their country specific de-identified and pseudo-anonymised data.

Information Governance

No identifiable information will be collected. No individual medical school data will be published with the exception of case studies with permission from the medical school. Data will be collected using a structured standard questionnaire. All data will be pseudo-anonymised. Providing personally identifying data (i.e. contact details) will be optional and will not be linked to the questionnaire answers given. All other data collected may be used for research purposes. Data will be stored securely and accessible only by the primary researchers and users nominated by them. At the end of the project, the data will be stored for five years after final publication.

Statistical Analysis

The resultant data will be analysed via descriptive statistics. For quantitative data where possible, ANOVA tests will be used for parametric data and the Wilcoxon signed-rank test will be used for non-parametric data. For Likert scale data, a multinomial regression will be utilised.

Authorship

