**Conclusion**

The International Survey Of Medical students Exposure to Relevant global Surgery (ISOMERS) will establish whether medical students are exposed to global surgery during medical school, how they are exposed to global surgery, whether the types of exposures meet the needs of students, current global surgery knowledge among students, and career aspirations among students and doctors. This is the first such an endeavour has been undertaken internationally. Our results will allow us to draw comparisons between countries.

*Appendix S2*

PDF attachment

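### The protocol names a paired test, the Wilcoxon signed-rank, as the rank alternative to ANOVA, although the comparisons it announces are between independent groups

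*Protocol*

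**What the plan says.** The Statistical Analysis part of the protocol's Methods begins with descriptive statistics and then names three inferential methods. On parametric data it says: "For quantitative data where possible, ANOVA tests will be used for parametric data". The same sentence continues for the remaining quantitative data: "the Wilcoxon signed-rank test will be used for non-parametric data". Likert items are treated apart: "For Likert scale data, a multinomial regression will be utilised".

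Study Design says that the study "is an online, international, multi-centre, questionnaire-based study evaluating global surgery exposure and career aspirations among final year medical students across the world". Information Governance adds that giving contact details "will be optional and will not be linked to the questionnaire answers given". The Conclusion announces the use to which the data will be put: "Our results will allow us to draw comparisons between countries". The first primary outcome is also laid out by country: "The proportion of students that have had exposure to global surgery in each country".

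**The concern.** The sentence sets the signed-rank test beside ANOVA as what to use on the same kind of data when parametric assumptions fail. ANOVA, with no repeated-measures form mentioned, compares the means of independent groups. Its rank counterpart is the Kruskal-Wallis test, or the rank-sum test when there are two groups. The signed-rank test answers a different question: whether differences within matched pairs, or departures of one sample from a fixed value, are centred on zero.

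If the sentence is followed, the protocol offers no usable rank test for comparing a skewed quantitative variable between countries. The analysts would have to choose a substitute after seeing the data, or force unrelated students into pairs and report a p-value that depends on how the file happened to be sorted. The protocol promises a public anonymised dataset (Ethics and dissemination), so a reader who sorted the rows differently could obtain a different p-value from the same data.

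**Working it through.** **1. The protocol's own figure.** The only statistical figure in the protocol is the sample size, stated as "margin of error of 5% and a confidence level of 95% is 377 assuming a 50% response distribution for each question".
- Without a population limit: n = z²p(1−p)/e² = 1.96² × 0.25 / 0.05² = 384.1, rounded up to 385.
- With the finite population correction: n = N·z²p(1−p) / [(N−1)e² + z²p(1−p)]. The protocol gives no N. Assuming N = 20,000, n = 19,207 / 50.958 = 376.9, rounded up to 377, which matches.
- For N from 10,000 to 1,000,000 the result runs from 370 to 384.

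The figure rests on the precision of a proportion and does not involve the signed-rank test.

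**2. Is there anything to pair?**
- Study Design describes one questionnaire. No baseline and follow-up, no pre/post measurement and no matching appears anywhere. That each student answers once is inferred from this; the protocol does not say it in so many words.
- Information Governance separates contact details from answers, and no other key for linking two submissions is described.
- The groups announced are countries: different students, with nothing to make the numbers equal or limit them to two.

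**3. What the test needs.** The statistic is built from Dᵢ = Xᵢ − Yᵢ for matched i = 1…n: the |Dᵢ| are ranked and the ranks of the positive differences are summed.
- *Unequal groups.* Dᵢ is undefined for the unmatched students. A trial run with 10 against 12 values stopped with an error.
- *More than two groups.* There is no single set of differences. Taking countries two at a time only returns to the two-group problem.
- *Two equal groups.* The test runs, but which Y is subtracted from which X is arbitrary.

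**4. How arbitrary?** Simulated illustration, not trial data: two independent normal samples, 60 per group, SD 1, true shift 0.4 SD, with the second group re-ordered at random 2,000 times.

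| Test | p-value on the same data |
|---|---|
| Signed-rank, 2,000 pairings | 0.00007 to 0.070, median 0.014 |
| Rank-sum | 0.007 (one value) |

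In this data set 99.4% of pairings gave p < 0.05, so about 0.006 × 2,000 = 12 fell on the other side. The p-value varies widely; the verdict at 5% seldom flips here.

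**5. Long-run behaviour.** 3,000 simulated studies, 60 per group, arbitrary pairing:

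| | Signed-rank | Rank-sum |
|---|---|---|
| Rejection rate, no difference | 4.6% | 4.4% |
| Power, shift 0.5 SD | 75.0% | 75.7% |

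The simulation error at a true rate of 5% is √(0.05 × 0.95 / 3,000) = 0.4 percentage points, so neither null rate is distinguishable from 5%. This is expected: if the pairing is unrelated to the answers, differences between two identically distributed groups are symmetric about zero.

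**6. The replacement.** The Kruskal-Wallis test ran without difficulty on three simulated groups of 20, 50 and 90.

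**The case against.** The strongest reply is that little in the study depends on this sentence. The primary outcomes are a proportion by country, a range of modalities and a percentage preferring each; the secondary outcomes are two proportions and a range of barriers. The section puts descriptive statistics first, and no hypothesis is stated. The Conclusion's remark on countries names neither a variable nor a test, and the one outcome laid out by country is a proportion, for which none of the rank tests is the natural choice. All of this stands, and it limits the point to inferential comparisons of quantitative variables that the protocol does not name.

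It can also be said that a paired use may exist. The questionnaire is not visible (Appendix S2 is only an attachment), and the Conclusion asks whether exposure matches what students need, which might set two answers from one respondent side by side. The signed-rank test could be right there. But no such quantitative comparison is described, so this does not rescue the sentence as written.

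Three stronger readings are tempting and are not supported:
- *Every rank-based comparison fails.* This cannot be shown without the questionnaire.
- *The false-positive rate is inflated.* The check in step 5 found no inflation.
- *The main results are compromised.* The listed outcomes do not use the test.

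The matter cannot be left to a statistical analysis plan, because the protocol fixes the test by name. If it is a slip for rank-sum, the text still needs correcting, and rank-sum alone would not cover more than two countries.

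**Conclusion.** The point holds, with limited reach. The protocol names a paired or one-sample test where the design it describes calls for a test of independent groups. For between-country comparisons of non-Likert quantitative data, the named test either cannot be computed (unequal sizes, or more than two groups) or, with two equal groups, gives a p-value that depends on arbitrary row order. The fault is arbitrariness or non-computability, not loss of type I error control.

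The descriptive primary and secondary outcomes, the Likert analyses and the sample size of 377 are untouched. Severity is moderate.

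The conclusion assumes that each student contributes one response, that ANOVA is meant in its between-group form, and that at least one quantitative variable will be compared between groups. The absence of type I inflation assumes that row order is unrelated to the answers. The size of the p-value spread belongs to the simulated example (normal data, 60 per group) and is not a forecast for this study.

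**What to change.** In the Statistical Analysis section, replace the clause on the signed-rank test with wording such as: for quantitative data that do not meet parametric assumptions, independent groups will be compared with the Kruskal-Wallis test when there are more than two and with the Wilcoxon rank-sum (Mann-Whitney) test when there are two; the Wilcoxon signed-rank test will be used only to compare two quantitative items answered by the same respondent. If no within-respondent comparison is intended, the last clause can be dropped.

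The cost is one sentence. Data collection, the questionnaire and the sample size do not change. The change is best made before data are analysed, so that the test is not chosen with the results in view. It covers quantitative variables only and is not meant for the exposure proportions by country.

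### Multinomial regression for Likert items ignores the order of the answers and costs about 20 percentage points of power when differences run in one direction

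*Protocol*

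**What the plan says.** In the protocol's Methods, the Statistical Analysis paragraph begins with "The resultant data will be analysed via descriptive statistics". It then names tests for quantitative data and ends with "For Likert scale data, a multinomial regression will be utilised". No predictors, ordinal variant or reason for the choice is given.

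The Data collection paragraphs of the same section say: "The online questionnaire utilises a combination of the Likert scale, multiple choice options and free text questions". Likert items and multiple-choice items are thus listed as different types, and the nominal model is assigned to the Likert items. The number of Likert points is not stated.

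Two other statements bear on the size of the problem. The Study Population paragraph gives the minimum sample for a "margin of error of 5% and a confidence level of 95% is 377 assuming a 50% response distribution for each question". The Conclusion adds: "Our results will allow us to draw comparisons between countries".

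**The concern.** The answers to a Likert item run from one pole to the other. A multinomial logit does not use that order: relabelling the categories in any sequence gives the same fit. It estimates a separate contrast for every category against a reference, so a single shift towards agreement is spread over several coefficients and tested on several degrees of freedom.

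Three things follow. A real one-directional difference in attitude is more likely to be missed. Each comparison is reported as several odds ratios instead of one. And if the predictor has many levels, as country would, the number of coefficients grows quickly against a sample that was sized for the precision of one overall proportion.

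The protocol fixes this method outright, so it is not a detail left to a SAP.

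**Working it through.** **The protocol's own figure.** The usual formula for a proportion gives 1.96² × 0.5 × 0.5 / 0.05² = 384.1, so 385 for an infinite population. With a finite population correction and N = 20,000, 384.1 / (1 + 383.1/20,000) = 376.9, so 377. The protocol does not state N, but any N from about 17,700 to 20,200 gives 377. The figure reproduces. It concerns one proportion, not a regression.

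**Coefficients.** Let K be the number of answer categories and C the number of levels of a predictor. The multinomial model needs (K-1)(C-1) coefficients for that predictor and the proportional-odds model C-1. The ratio is K-1 whatever C is: 2 for K = 3, 3 for K = 4, 4 for K = 5 and 6 for K = 7.

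**Power for a one-directional difference.** Assumptions, none of them in the protocol: a five-point item, base probabilities 0.10/0.20/0.30/0.25/0.15, a common odds ratio across cut-points and two-sided 5% significance. The comparison is simulated, with a rank test (equivalent to the proportional-odds score test) against the multinomial likelihood-ratio test.

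| Setting | Ordinal | Multinomial |
|---|---|---|
| 100 per group, odds ratio 2.0 | 78% | 58% |
| 150 per group, odds ratio 1.75 | 77% | 56% |

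A noncentral chi-square calculation at 377 responses in total, with category probabilities 10/20/40/20/10%, agrees. Two groups at odds ratio 1.65 give 76% against 55%. Ten equal countries whose log-odds vary with standard deviation 0.4 give 85% against 58%.

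**Sparsity, if country is the predictor.** Assumptions: K = 5, 377 responses split equally over C countries, the base probabilities above and no true difference.

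- Responses per multinomial country coefficient = 377 / [4(C-1)].
- Expected empty cells = C × Σ(1-p)^(377/C), summed over the five category probabilities p. For C = 20 this is 20 × (0.90^18.85 + 0.85^18.85 + 0.80^18.85 + 0.75^18.85 + 0.70^18.85) = 4.1.
- False rejection is the simulated share of data sets in which the nominal likelihood-ratio test has p < 0.05.

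| Countries | Responses per coefficient | Expected empty cells | False rejection |
|---|---|---|---|
| 10 | 377/36 = 10.5 | 0.2 of 50 | about 7% |
| 20 | 377/76 = 5.0 | 4 of 100 | about 16% |
| 40 | 377/156 = 2.4 | 32 of 200 | about 42% |

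With 2 countries there are 94 responses per coefficient and with 5 there are 24; the test then stays close to its nominal level. The rank-based ordinal test stayed at about 4 to 5% throughout.

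**The reverse case.** Take two groups, 377 responses in total, one answering 10/20/40/20/10% and the other 20% in every category. The second group is more polarised, but its centre has not moved. The multinomial test detects this with 99.6% power and the ordinal test with 4.8%.

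**The case against.** Multinomial regression is a valid model. It needs no proportional-odds assumption, and the power figures above assume the condition that most favours the ordinal model; in the polarised example the ranking reverses. This stands. It is the reason to check the assumption and keep a fallback, but not a reason to make the nominal model the default for ordered answers.

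The listed primary and secondary outcomes are proportions, percentages and ranges, and the analysis is descriptive first. No outcome is tied to a Likert item. The country-level primary outcome is "The proportion of students that have had exposure to global surgery in each country", which is not said to be a Likert item. This stands too: the loss falls on supporting analyses.

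A reader might infer that the plan fits about four times as many country coefficients as the data can support. The document does not show that. Four is K-1 for a five-point item, relative to a proportional-odds model, and says nothing about what 377 responses can carry. The number of categories, the number of countries and the covariates are all unstated. The Conclusion expects comparisons between countries but does not say that this regression makes them, and 377 is a minimum for a survey open worldwide. With few countries the multinomial model is supportable.

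Finally, an ordinal model does not rescue very small country samples. With 20 countries and a log-odds standard deviation of 0.3, its power at 377 responses is only 42%, against 21% for the nominal model.

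**Conclusion.** The concern holds in a limited form. The protocol prescribes a model that discards the order of Likert answers, without giving a reason. Its cost is K-1 coefficients per predictor level instead of one and, for one-directional differences under roughly proportional odds, about 20 percentage points of power. Those power figures rest on an assumed five-point item and assumed category probabilities and effect sizes.

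Inflated false rejection is conditional: it arises only if the same model compares many countries near the minimum sample, and it becomes serious at about 20 countries or more. Nothing here suggests that the descriptive primary results are wrong. This is a cheap improvement to supporting analyses.

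**What to change.** Replace the sentence on Likert data with one that does the following:

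- makes ordinal (cumulative-logit) regression the main model for Likert items;
- requires the proportional-odds assumption to be checked, with a partial proportional-odds or multinomial model where it clearly fails, since an ordinal test can miss polarised answers;
- keeps multinomial regression for unordered items such as preferred modality.

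If countries are to be compared on Likert items, also state whether country enters the model. With many small countries, group them into regions or use a random effect, because the change of link alone does not solve small samples.

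The cost is a sentence or two, with no change to the questionnaire or to data collection. The downside is that the proportional-odds assumption must be checked and the check reported. The change should be made before the data are seen, so that the model is not chosen by its results.

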**Ethics and dissemination**

Ethics

Ethical exemption received from the Universite Technologique, “Bel Campus”, University of Technology

Dissemination

The protocol will be disseminated primarily through recruited medical student collaborators. Should medical schools wish to see the protocol, collaborators may pass it along as well.

The survey findings will be presented at local, regional, national, and international conferences by medical student collaborators. A standard PowerPoint presentation and poster will be created for this purpose. All presentations will be coordinated by the ISOMERS steering committee to avoid duplications and to ensure all conference regulations are fulfilled. In addition, the results will be disseminated via publication in a peer-reviewed medical journal. All collaborators will be co-authors of resulting presentations and PubMed Citable co-authors of resulting publication(s).

Following publication, the manuscript can be shared by collaborators with their medical schools to feedback the study results. Medical schools can request for their own specific data and the analysis done on said data from the ISOMERS steering committee following study completion. The fully anonymised dataset will be made publicly available.

**Project Timeline**

|  | **September** | **October** | **November** | **December** | **January** |
| --- | --- | --- | --- | --- | --- |
| Regional Lead Recruitment |  |  |  |  |  |
| Data collection |  |  |  |  |  |
| Data analysis |  |  |  |  |  |
| Manuscript preparation |  |  |  |  |  |

**Table 1:**Project timeline. Extended data collection periods may be incorporated to grant flexibility to centres that may have experienced logistical obstacles to study commencement.

**Conclusion**

The International Survey Of Medical students Exposure to Relevant global Surgery (ISOMERS) will establish whether medical students are exposed to global surgery during medical school, how they are exposed to global surgery, whether the types of exposures meet the needs of students, current global surgery knowledge among students, and career aspirations among students and doctors. This is the first such an endeavour has been undertaken internationally. Our results will allow us to draw comparisons between countries.

*Appendix S2*

PDF attachment
